### 3.5.2 Study Limitations

#### Drug Shortages

A known limitation of this study is that there were drug shortages among the antibiotics of interest while the study was ongoing. This means that differences observed between the two interventions, or the lack of differences observed may be related to drug availability and not the intervention.

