## 4 STUDY DESIGN

This study is a three-stage cluster randomized historically controlled crossover trial designed to evaluate the feasibility of the implementation of two AS strategies. Data will be obtained from four community hospitals in three stages. In stage 1, historical data from each hospital will be collected for the year prior to study initiation from all participating hospitals. These data are used as a control representing current practice. In stage 2, the four hospitals will be divided into two pairs based upon bed size. One hospital from each pair will be randomly assigned to a six-month period of antimicrobial restriction and preauthorization (Strategy 1; stage 2) followed by a six-month period of post-antibiotic prescription review (Strategy 2; stage 3). The other two hospitals will undergo Strategy 2 in stage 2 followed by Strategy 1 in stage 3 to help alleviate the concern for seasonal/temporal effects when comparing the strategies to each other. Temporal/seasonal effects are not controlled when comparing to the historical control. A one-month wash out will be performed between each stage. Three antibiotics will be specifically targeted for intervention: anti-pseudomonal carbapenem of choice at the study hospital, vancomycin, and piperacillin-tazobactam. Utilization of alternative antimicrobials, including fluoroquinolones, cephalosporins, and anti-methicillin-resistant *Staphylococcus aureus* (anti-MRSA) systemic antimicrobials (e.g., nafcillin, daptomycin, linezolid, ceftaroline, clindamycin, and trimethoprim-sulfamethoxazole [TMP-SMX]) will also be collected.

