#### Secondary Stewardship Hypotheses

1. Antimicrobial restriction and preauthorization will be less resource-intensive for hospitals (e.g., set-up time, approval time, personnel resources) than post-antibiotic prescription review (PAR) and feedback.
2. Prescribers will consider preauthorization to be intrusive to clinician autonomy and patient care.
3. The cost of performing PAR by a trained pharmacist will be offset by the cost savings achieved by decreasing antimicrobial cost.
4. Both strategies will lead to a decrease in utilization for targeted antimicrobials relative to utilization in the period prior to implementation of the stewardship strategies.
5. Decreases in targeted antimicrobial utilization from antimicrobial restriction will be offset by increases in use of alternative antibiotics.
6. The strategy of antimicrobial restriction and preauthorization will be less effective at reducing overall antimicrobial use than the strategy of prospective audit and feedback, as it will not shorten duration of antimicrobial therapy.

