## 3.5 General statistical considerations

- Tables will be presented by Hospital and intervention; each of the 4 sites will be evaluated separately.
  - Stratified pooled analyses may also be conducted
- Dates will not be shown, but converted to days from intervention (intervention) or first hospital contact (feasibility).
- Each Table/Figure/Listing will be annotated with the name and location of the program used to create it, including its location directory.
- All programs that create permanent study-specific derived datasets or that contribute to analyses of the primary or secondary objectives will be validated according to CBAR SOPs
- Categorical variables will be summarized with n and proportion
- Continuous variables will be summarized with mean, sd, median, Q1, Q3, min and max.
- For secondary analyses, there are 3 contrasts of interest
  - PAR vs. historical control
  - Formulary Restriction/Preauthorization (Res/PreA) vs historical control
  - PAR vs Res/PreA
- For each contrast, the difference in outcomes will be estimated using 95% confidence intervals
  - Difference in proportion with 95% CIs for binary outcomes
  - Difference in means with 95% CIs for continuous outcomes

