408         than one intervention over the course of a year)

409 Signs and symptoms

410     • Fever

411     • Leukocytosis

412     • Hypotension

413     • Cough or Sputum production

414     • Other signs or symptoms

- 415 • List of other/specifies
- 416 • Number of signs and symptoms per intervention

417 Culture data

- 418 • Culture data available for review (yes/no)
- 419 • If yes, was the culture data reviewed
- 420 • If yes, did it help inform the recommendation?

421 Intervention outcome

- 422 • Was the recommendation followed?
- 423 • Was there an ID consult after the intervention?
- 424 • ICU admission

425 Ultimate Infection diagnosis related to recommendation

- 426 • Pneumonia
- 427 • UTI
- 428 • Meningitis
- 429 • Surgical site infection
- 430 • SSTI
- 431 • Colitis
- 432 • Bacteremia
- 433 • Sepsis with unknown source
- 434 • No infection
- 435 • Other
- 436 • List of other, specify

437 **10. Days Of Therapy**

438 **Purpose:** To address Secondary objective 2, to compare DOT for antibiotics of interest between each  
439 strategy.

440

- 441 • Days of therapy (DOT) for targeted and alternative antibiotics
  - 442 ○ Per the protocol, DOT will be measured as the number of days a patient receives
  - 443 each targeted and alternative antibiotic during the hospital admission

444 The three targeted antibiotics are:

- 445 • Anti-pseudomonal carbapenem of choice at the study hospital
- 446 • Vancomycin
- 447 • Piperacillin-tazobactam.

448 The alternative antimicrobials of interest are:

- 449 • Fluoroquinolones
- 450 • Cephalosporins
- 451 • anti-MRSA systemic antimicrobials (e.g., nafcillin, daptomycin, linezolid, ceftaroline,
- 452 clindamycin, and TMP-SMX).

Among admissions with an included antibiotic, by hospital

- Table 1
  - Year prior to study
  - Period 1 Admission with Included antibiotic, no intervention
  - Period 1 Admission with stewardship intervention
  - Period 2 admission with Included antibiotic, no intervention
  - Period 2 admission with stewardship intervention
- Table 2
  - Period 1 (all admissions with an antibiotic of interest)
  - Period 2 (all admissions with an antibiotic of interest)
- Table 3
  - For 3 contrasts (PAR vs Historical year; Res/PreA vs historical Year; PAR vs Res/PreA)
  - Difference in proportion used drug with 95%CI
  - Difference in Mean DOT with 95% CI

For each antibiotic,

- proportion of admissions where the antibiotic was received
- DOT for the antibiotic

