  - Admissions where the antibiotic was not received will have a DOT of 0.
- Modeling (1 model for each of the antibiotics of interest)
  - The purpose of the model is to look at the effect of the intervention on DOT for each antibiotic of interest
  - Dependent variable = DOT for each antibiotic
  - Adjusting for hospital, study period, AS strategy, calendar time, demographic variables
  - The interactions of study period \* strategy, hospital \* study period, hospital \* strategy, will be explored.

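### Drug shortages during the study are disclosed but enter no days-of-therapy (DOT) analysis, so the by-hospital and historical contrasts cannot tell a shortage from a strategy effect

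*Combined protocol and SAP*

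**What the plan says.** SAP 3.5.2 states that "there were drug shortages among the antibiotics of interest while the study was ongoing" and draws the consequence itself: "differences observed between the two interventions, or the lack of differences observed may be related to drug availability and not the intervention". It does not say which drugs, hospitals or dates were affected, or whether the historical year was free of shortage. The only other mention is in SAP 12, where the antibiotic cost analysis is deferred partly because of the shortages.

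The DOT analyses are in SAP 10. Table 3 gives differences in the proportion who used each drug and in mean DOT, "For 3 contrasts (PAR vs Historical year; Res/PreA vs historical Year; PAR vs Res/PreA"), with no adjustment listed. SAP 3.5 says that "each of the 4 sites will be evaluated separately" and makes stratified pooling optional. SAP 10 also plans one model per antibiotic: "Adjusting for hospital, study period, AS strategy, calendar time, demographic variables". It adds: "The interactions of study period \* strategy, hospital \* study period, hospital \* strategy, will be explored". Protocol 9.4.1.3 has a model with treatment, period, site and period-by-site. Neither model has a shortage term.

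Protocol 4 says of the historical year: "These data are used as a control representing current practice". Hypothesis 4 predicts that use of targeted drugs falls under both strategies relative to the time before them. Hypothesis 5 reads: "Decreases in targeted antimicrobial utilization from antimicrobial restriction will be offset by increases in use of alternative antibiotics".

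**The concern.** The contrasts treat PAR, preauthorization and the historical year as conditions that differ in stewardship. If a drug was hard to obtain in one of them, they also differ in supply, and a fall in its use has two possible causes. The SAP recognises this but plans no analysis that would show how much of a difference belongs to which cause. The data sources in protocol 9.4.2 and 16.2 do not include shortage dates, so unless they are requested the caveat cannot be checked later.

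At stake is the reading of the drug-level secondary results. Suppose a targeted drug was short during the study but not in the historical year, and prescribers moved to alternatives. The unadjusted contrasts could then show a fall in targeted use and a rise in alternatives with no strategy effect, which is the pattern of hypotheses 4 and 5. A shortage could equally hide a real difference between strategies.

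**Working it through.** **1. The plan's own figure.** Protocol 9.1 gives 97% power for 0.50 against a 0.05 difference, with 3,000 patients per period and alpha 0.05 (taken as two-sided). SE = √[p1(1−p1)/n + p2(1−p2)/n] = √[(0.2500 + 0.2475)/3,000] = 0.01288. Then z = 0.05/0.01288 = 3.88, and Φ(3.88 − 1.96) = 0.973. The figure is reproduced.

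**2. By-hospital contrasts with no strategy effect.** Shift = p × (shortage days/180) × fractional cut in use. The 180 days come from the dates in SAP 6, reading both printed end years as 2015 (6 Oct 2014 to 3 Apr 2015; 4 May to 30 Oct 2015). Length and depth of shortage are assumed. For 18 days:

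| Baseline p | Cut in use | Shift | CI excludes 0, n = 3,000 | n = 1,000 |
|---|---|---|---|---|
| 0.50 | full | 0.50 × 0.1 × 1 = 5.0 points | 97% | 61% |
| 0.50 | half | 0.50 × 0.1 × 0.5 = 2.5 points | 49% | 20% |
| 0.20 | full | 0.20 × 0.1 × 1 = 2.0 points | 51% | 21% |
| 0.20 | half | 0.20 × 0.1 × 0.5 = 1.0 point | 16% | 9% |

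For example, the second row at n = 3,000 has SE = √[(0.2500 + 0.2494)/3,000] = 0.01290 and z = 0.025/0.01290 = 1.94, hence 49%. A longer shortage gives more: 0.20 halved for three of six months shifts by 0.20 × 0.5 × 0.5 = 5.0 points, and the interval excludes zero 99.9% of the time at n = 3,000 (55% to 95% at 500 to 1,500).

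**3. Pooled PAR minus preauthorization.** Assume a shortage lowers mean DOT by 0.5 in each affected month and lasts three of the six months of period 2. The period-2 mean at an affected hospital falls by 0.5 × 3/6 = 0.25. In the sequence preauthorization then PAR, the hospital's PAR minus preauthorization difference is −0.25; in the other sequence it is +0.25. Averaging over the four hospitals:

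- all four affected: (−0.25 + 0.25 + 0.25 − 0.25)/4 = 0
- both hospitals of one pair: (−0.25 + 0.25 + 0 + 0)/4 = 0
- both hospitals of the sequence ending in PAR: (−0.25 + 0 + 0 − 0.25)/4 = −0.125
- one hospital of that sequence: −0.25/4 = −0.0625

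Least squares on noise-free hospital-by-month means gives the same values. Adding period, linear time or month dummies leaves −0.125 and −0.0625 unchanged.

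**4. Either strategy against history.** With all four hospitals affected as in step 3, each strategy has two of its four hospital-periods in period 2, so its bias is (−0.25 − 0.25 + 0 + 0)/4 = −0.125. If the shortage runs through the whole prospective phase the bias is −0.5.

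Study period cannot correct this: the two period indicators sum to the same column as the two strategy indicators (rank 8 of 9 columns with hospital and linear time; with month dummies, 28 of 29). A linear time term changed −0.125 to +0.048 for a three-month shortage in months 2 to 4 of period 2, a reversed sign. It left −0.5 unchanged for the whole-phase shortage.

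**5. With a shortage indicator.** A hospital-by-month indicator brought the spurious effect to 0 in every part-period scenario tested, for all three contrasts. If the shortage covers every prospective month at all four hospitals, the indicator cannot be separated from strategy against history (rank 7 of 8), and no model term helps.

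**The case against.** The plan is candid. It tells readers that a difference may reflect supply, the primary analysis is descriptive feasibility and is untouched, hypothesis testing in the secondary analyses is optional, and no rule exists for declaring hypothesis 4 or 5 supported. It also lets the shortages bear on the cost analysis. All of that stands and limits how serious the point is. It does not help a reader judge a particular DOT contrast.

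The model is not bare either. It has period and calendar time, it is fitted separately for each antibiotic (so timing that differs between drugs is no objection to its time term), and a hospital-by-period interaction will be explored. But common time terms do not follow a site-specific shortage. Hospital-by-period as a fixed effect is collinear with strategy in the prospective data (rank 9 of 10). The protocol's random period-by-site effect allows for site-specific disruption as added variance, but it does not identify a shortage.

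A reader might infer that the crossover protects the head-to-head comparison only if all four hospitals are hit alike. The design does not support that: each pair has one hospital on each strategy in each period, so an equal shortage within a pair also cancels.

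A reader might also infer that the shortages did produce the pattern of hypotheses 4 and 5. The documents do not support this. It needs a targeted drug in shortage, substitution, and an unaffected historical year, and none of these is stated. The antibiotics of interest include the alternatives, and a shortage of an alternative would push the other way. In the model with linear time, the hypothesis 4 pattern need not appear even then.

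**Conclusion.** The concern holds for the by-hospital Table 3 contrasts and for either strategy against the historical year: as planned, they cannot separate a shortage from a strategy effect. It holds for a pooled PAR against preauthorization estimate only where a shortage differs by site or sequence in a way that does not balance within pairs.

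The size is an assumed range. For an 18-day shortage at p = 0.50, the chance that the interval excludes zero with no strategy effect runs from about 49% to 97% at 3,000 per period, and from about 20% to 61% at 1,000. The 97% should not be taken as typical. It is the case of complete unavailability at a proportion that protocol 9.1 offers as an example for patients with no DOT, not for use of one drug. The 3,000 comes from expected admissions, whereas SAP 10 analyses admissions with an included antibiotic. The protocol's power figure itself is correct on its inputs.

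This should be changed. It does not threaten the primary feasibility result.

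**What to change.** In SAP 10:

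1. Obtain from each hospital pharmacy the start and stop dates of shortage for each antibiotic of interest, for the historical year and both study periods. Fix these dates without reference to DOT results.
2. Add a hospital- and drug-specific shortage indicator, by admission date or month, to each drug's DOT model. In the models for alternatives, add an indicator that a targeted drug was short. State a rule for admissions that straddle a shortage.
3. As a sensitivity analysis beside the full-period Table 3, show contrasts that exclude the affected dates. Remove matching calendar dates only for the historical contrasts: the two study periods share calendar dates only in October, so matching is not workable for PAR against preauthorization.
4. Where a shortage covers a whole period at a hospital, report that drug's contrast there as not attributable to the strategy.

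Report both sets of results and say whether the reading of hypotheses 4 and 5 depends on the shortage dates. Agreement between the two should not be required, since a full-period result biased by a shortage would then override the corrected one.

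The cost is a SAP revision, a date request to four pharmacies, an added covariate per model and a repeat table per drug. Intervals will be wider where dates are removed, and the result depends on how well each pharmacy recorded its shortages.

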#### Study Design

The study design has limitations. First, the study is essentially non-randomized. Even randomization of hospitals cannot guarantee the balance of confounding factors on the unit of analyses (patients). The cross-over design helps to alleviate this concern as each hospital would be expected to enroll similar populations into each intervention period.

Second, our designed strategies may miss intervention opportunities. Our study design includes pharmacist interventions during business hours on Monday through Friday and does not include weekend interventions. This inclusion criterion will impact Strategy 1 more than Strategy 2, as no alternative approach is available for Strategy 1. To overcome this limitation for Strategy 2, we will allow the intervention to occur within 72 hours of prescription  $\pm$  24 hours, if necessary. This window for intervention will be adequate to intervene on all antibiotic prescriptions. We believe that this approach is appropriate, as we suspect this approach is likely to mirror how most hospitals will eventually implement each of these interventions; thus, it is more likely to lead to true conclusions regarding the feasibility and outcomes of each of these interventions.

Third, the short study period and limited study sites will hinder our ability to demonstrate definitive changes in our secondary analyses, including changes in antimicrobial utilization. The primary goal of this study, however, is to assess feasibility. An additional limitation to the short study period, is that there may be temporal effect that will differ across the two study periods

Next, the effectiveness of any stewardship program is likely to vary depending on the experience and expertise of the pharmacist performing the PAR and local hospital culture.

As the primary control group is historical, subsequent comparisons may be biased by temporal effects. The crossover nature of the trial design helps to alleviate this bias inherent to comparing the AS interventions in pooled analyses.

Lastly, DOT is limited to the duration of hospitalization, which ends upon discharge or death.

#### 4. Feasibility Analyses

**Purpose:** to address the primary feasibility objectives

Summary of REDCap data - Listings by hospital

Approval Information

- Days from Date of initial discussion to date intervention approved
- Met with Pharmacy leadership (y/n)
- Days from initial discussion to Pharmacy Leadership Meeting
- Met with PT committee (y/n)
- Days from initial discussion to PT committee meeting
- Met with hospital administration (y/n)
- Days from initial discussion to Hospital Administration Meeting
- Met with medical executive committee (y/n)
- Days from initial discussion to Medical Executive Meetings
- Met with other (specify) (y/n)
- Days from initial discussion to Other meeting

Hospital Size

- Hospital bed size
- Hospital average patient days (per year) (confirm that this is per year and not per month)

IT Set -Up Time

- IT time required to set up lists

Pharmacist Training, by Hospital

- Number of Pharmacists trained
- Mean Pharmacist training time (hours)

Treatment Assignment – Study period for each Stewardship Strategy, by hospital

- PAR assignments
- Restriction/Pre-Authorization assignments

#### 5. Pharmacist Time (Resource utilization)

**Purpose:** to summarize pharmacist time by hospital and stewardship strategy. Addresses secondary objective 1, resource utilization of each strategy where resource utilization includes pharmacist time.

- Listing of hours per week by hospital for study period 1 and study period 2.
- Summary, by hospital, of hours per week for period 1 and period 2

#### 6. Hospital Admissions

**Purpose:** To summarize hospital admissions over the time periods of interest.

Hospital Admissions Tables, by hospital

a. Number of unique admissions by hospital

1. In the year preceding the start of the study period 1 (October 6, 2013 through October 5, 2014)
2. Study period 1 (October 6, 2014 through April 3, 2014)
3. Study period 2 (May 4, 2015 through October 30, 2014)

b. Number of admissions by hospital that received an “Included antibiotic” or “other antibiotic”

1. In the year preceding the start of the study period 1 (October 6, 2013 through October 5, 2014)
2. Study period 1 (October 6, 2014 through April 3, 2014)
3. Study period 2 (May 4, 2015 through October 30, 2014)

c. Number of admissions by hospital that received an “Included antibiotic”

1. In the year preceding the start of the study period 1 (October 6, 2013 through October 5, 2014)
2. Study period 1 (October 6, 2014 through April 3, 2014)
3. Study period 2 (May 4, 2015 through October 30, 2014)

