#### 9.4.1.3 Discussion of cluster randomized design and the key secondary analysis

This antimicrobial stewardship study will be implemented at four hospitals, where each hospital is considered a single cluster. The four hospitals participating in this study will be paired by size. One hospital in each pair will receive Strategy 1 followed by Strategy 2, while the other hospital in each pair will receive Strategy 2 followed by Strategy 1. The ordering within each pair will be randomly assigned.

Cluster randomized trials can be analyzed at the cluster level or the patient level. Ideally, analyses are conducted on the cluster level as this is the unit of randomization. However, we will analyze this study using the patient as the unit of analyses as there are only four clusters.

Since randomization occurs at the cluster level but analyses must be conducted at the patient level, the benefits of randomization (i.e., expectation of balance of confounding factors) cannot be assumed. The small sample size of 4 clusters may also negate the benefits of randomization. The crossover nature of the design will help to balance confounding factors as each hospital can serve as its own control. However, as the crossover occurs at the cluster level, and the patients are neither randomized nor crossed-over, it does not have the same advantages as a standard crossover trial and it does not eliminate within-patient variation; the analyses cannot be “paired”.

Since the effect of the intervention is not only a function of the intervention itself but also of the pharmacist, there is potential for considerable site variation in response. Thus each of the four sites will be evaluated separately. Stratified pooled analyses may also be conducted.

For each site and each contrast (Intervention 1 vs. control; Intervention 2 vs. control; and Intervention 1 vs. Intervention 2), the difference in outcomes will be estimated using 95% confidence intervals. Examples for binary and continuous outcomes are displayed in Figure 9-2 and Figure 9-3, respectively.

Figure 9-2

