## 16 DATA HANDLING AND RECORD KEEPING

### 16.1 Data Management Responsibilities

The hospitals will enter data into the ARLG DICON1 database via Research Electronic Data Capture (REDCap; see Data Capture Methods below). Other data will come from the ARLG DICON1 EHR database. DICON Network personnel will reconcile the data, strip out the MRN identifiers, and provide DCRI with an ARLG DICON1 limited database with the DICON ID as the subject identifier. These limited datasets will be sent to DCRI as the data coordinating center. DCRI will send the data to the Harvard Statistical Center for analysis.

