#### **13. Patient specific outcomes between each strategy**

**Purpose:** to address secondary objective 3, to compare patient-specific outcomes between each strategy, including but not limited to the following:

494 a. Total hospital days

495 b. Intensive care unit admission

496 Each of Total hospital days, death, and ICU admission will be summarized by hospital in 3 tables:

497 Among admissions with an included antibiotic

498 • Table 1

499 ○ Year prior to study

500 ○ Period 1 Admission with Included antibiotic, no intervention

501 ○ Period 1 Admission with stewardship intervention

502 ○ Period 2 admission with Included antibiotic, no intervention

503 ○ Period 2 admission with stewardship intervention

504 • Table 2

505 ○ Period 1 (all admissions with an antibiotic of interest)

506 ○ Period 2 (all admissions with an antibiotic of interest)

507 • Table 3

508 ○ For 3 contrasts (PAR vs Historical year; Res/PreA vs historical Year; PAR vs Res/PreA)

509 ○ Difference in proportion of ICU admissions with 95%CI

510 ○ Difference in Mean total hospital days with 95% CI

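### The plan names the patient as the unit of analysis but analyses admissions, and does not say how repeat admissions enter the secondary site-level 95% CIs

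*Combined protocol and SAP*

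**What the plan says.** Protocol 9.4.1.3 and SAP 3.5.1 use the same sentence: "we will analyze this study using the patient as the unit of analyses as there are only four clusters".

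The SAP sections that produce results use a different unit:

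- SAP 6 is a count table: "Number of unique admissions by hospital".
- SAP 10 (Days Of Therapy) reports, for each antibiotic, the "proportion of admissions where the antibiotic was received", and sets the zero rule: "Admissions where the antibiotic was not received will have a DOT of 0".
- SAP 13 tabulates hospital days, death and ICU admission "Among admissions with an included antibiotic".

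On method, SAP 3.5 says that for each contrast "the difference in outcomes will be estimated using 95% confidence intervals", as a difference in proportions for binary outcomes and a difference in means for continuous ones, with each hospital evaluated separately. No variance estimator is named. The protocol's heterogeneity model (9.4.1.3) has random effects for site and period-by-site only. The DOT models in SAP 10 adjust for hospital, period, strategy, calendar time and demographics, with no patient term.

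The SAP knows that people recur. Section 7 tabulates interventions per patient, and section 9 notes that one person may have several interventions in a year. Protocol 16.1 says the analysis database is supplied "with the DICON ID as the subject identifier", and 16.2 confirms that this ID identifies individual patients.

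**The concern.** A programmer cannot follow both instructions. Mean DOT per admission gives frequently readmitted patients more weight than mean DOT per patient, so the two units define different quantities as well as different variances.

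If admissions are the records and the ordinary two-sample formulas are used, each admission counts as an independent observation. Two admissions of one patient are likely to resemble each other in antibiotic choice, length of stay and ICU use. Within a period this makes the naive interval too narrow. A patient admitted in both compared periods induces positive correlation between the two arms, which makes the naive interval too wide. The net error has no fixed sign, and the plan gives no means of handling either part.

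At stake is the precision of the secondary per-site contrasts in SAP 10 and 13. Within one site there is a single period per strategy, so hospital-by-period variation cannot be estimated there. Dependence between admissions of the same patient can be.

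**Working it through.** **1. The plan's own figure.** Protocol 9.1 states 97% power within a hospital: 3000 per period, proportion 0.50, difference 0.05, alpha 0.05.

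- Null SE = √(2 × 0.475 × 0.525 / 3000) = 0.01289.
- Alternative SE = √((0.25 + 0.2475) / 3000) = 0.01288.
- Power = Φ((0.05 − 1.96 × 0.01289) / 0.01288) = Φ(1.920) = 0.9726.

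The figure reproduces, two-sided, with 3000 independent records. The naive 95% CI half-width is 1.96 × 0.01288 = 0.0252.

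**2. Repeats within a period.** The inputs are assumptions, because the documents give neither. Mean admissions per patient per period, m, runs from 1.05 to 1.5 (geometric); within-patient correlation, ρ, runs from 0.1 to 0.5. The design effect is DEFF = 1 + ρ(E[k²]/E[k] − 1), where k is a patient's number of admissions. For a geometric count E[k²]/E[k] = 2m − 1, so DEFF = 1 + 2ρ(m − 1). The correct CI is √DEFF times the naive width, naive coverage is 2Φ(1.96/√DEFF) − 1, and effective n is 3000/DEFF.

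| m | ρ | DEFF | CI width ratio | Half-width | Naive coverage | Effective n | Power |
|---|---|---|---|---|---|---|---|
| 1.05 | 0.1 | 1.01 | 1.005 | 0.0254 | 94.9% | 2970 | 97.1% |
| 1.2 | 0.3 | 1.12 | 1.058 | 0.0267 | 93.6% | 2679 | 95.6% |
| 1.3 | 0.3 | 1.18 | 1.086 | 0.0274 | 92.9% | 2542 | 94.7% |
| 1.5 | 0.3 | 1.30 | 1.140 | 0.0288 | 91.4% | 2308 | 92.5% |
| 1.5 | 0.5 | 1.50 | 1.225 | 0.0309 | 89.0% | 2000 | 88.6% |

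DEFF and coverage do not depend on n. The half-width, effective n and power columns are tied to the 3000 of Protocol 9.1. The distribution matters a little: with 1 + Poisson(0.3) admissions (mean 1.3), DEFF at ρ = 0.3 is 1.159 instead of 1.18.

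**3. Patients present in both compared periods.** With no within-period repeats and a share f of records belonging to such patients, the correct width is √(1 − fρ) times the naive width. For f from 5% to 20% and ρ from 0.1 to 0.5 this is 0.997 down to 0.949.

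**4. Both together.** Take two periods of equal length, the same ρ within and across periods, and a share c of patients seen in both. The covariance term adds −ρcm, so net DEFF = 1 + 2ρ(m − 1) − ρcm. With c = 0.20:

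- m = 1.05, ρ = 0.5: 1 + 0.05 − 0.105 = 0.945, coverage 95.6%.
- m = 1.2, ρ = 0.3: 1 + 0.12 − 0.072 = 1.048, coverage 94.4%.
- m = 1.5, ρ = 0.5: 1 + 0.50 − 0.15 = 1.35, coverage 90.8%.

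The two effects cancel at c = 2(m − 1)/m: 0.1/1.05 = 9.5% for m = 1.05, and 0.4/1.2 = 33% for m = 1.2. So the sign depends on how often patients return within a period relative to how many appear in both. For contrasts with the historical control the periods are 12 and 6 months, so m differs between arms and these equal-period figures are only indicative.

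**The case against.** The strongest reply is that patient in Protocol 9.4.1.3 and SAP 3.5.1 is set against hospital, not against admission. DOT is defined as days a patient receives a drug during the hospital admission, and Protocol 9.1 counts admitted patients. The word may simply be loose. That is a fair reading, but it leaves the unit unstated and still gives no rule for repeats.

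Second, the effect may be small. Repeats enter SAP 10 and 13 only when each admission had an included antibiotic, so all-cause readmission would overstate m. At the low end coverage is 94.9%, and cross-period overlap offsets part of the error. This stands, and it is why the point is minor.

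Third, clustering on patient does not make these intervals valid for the strategy effect. The temporal effects and drug shortages acknowledged in SAP 3.5.2 remain. This also stands.

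Four stronger readings are tempting and are not supported:

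- That the SAP departs from the protocol. SAP 3.5.1 repeats the protocol's sentence, so the mismatch is also inside the SAP.
- That the plan declares repeat admissions independent. It says nothing; independence is what the simple formulas would imply.
- That the count table in SAP 6 is at fault. It is descriptive, carries no CI, and counting admissions there is correct.
- That the trial's main result is affected. The primary analysis is a descriptive feasibility summary without testing (Protocol 9.4.1.1); the CIs are secondary.

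**Conclusion.** The point holds as a minor one about secondary analyses. The documents name one unit and analyse another, and they specify no first-admission rule, patient effect or clustered variance. CIs computed as written may have the wrong width, in a direction the documents cannot settle.

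Within-period repeats alone give a design effect of about 1.01 to 1.50 and naive coverage of about 94.9% down to 89.0%; mid-range (m = 1.2, ρ = 0.3) it is 93.6%. Cross-period overlap offsets part of this and, where within-period readmission is rare, can make the naive interval slightly conservative. All of these figures rest on assumed readmission rates, correlations and overlap. It cannot be said that the intervals are certainly wrong by a material amount; the loss is material only with frequent readmission and strong within-patient correlation.

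**What to change.** In SAP 3.5, 3.5.1, 10 and 13, state that the admission is the unit of analysis. Specify that all site-level CIs and model standard errors use patient-clustered variance on the DICON ID, by a sandwich estimator or by a bootstrap that resamples patients within hospital. Each patient's admissions from both compared periods must stay in one cluster, so that repeats within and across periods are both covered and the net direction need not be known beforehand. Add to SAP 6 the number of unique patients and the admissions per patient, by hospital and period, so that the size of the issue is visible. An analysis of the first admission per patient per period could serve as a sensitivity check on within-period repeats.

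The cost is a sentence in each section and one option in the analysis code; no new data are needed. CIs may widen slightly. The change does not address hospital-by-period variation, temporal effects or drug shortages, and the SAP should not suggest that it does.
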